## Section 1: Administrative information

### 1. Title and trial registration

#### 1a. Title:

Preparing and timing of the endometrium in modified natural cycle frozen-thawed embryo transfers (mNC-FET) - a randomized controlled multicentre trial

#### 1b. Trial registration:

Registered at ClinicalTrials.gov (NCT03795220) and EudraCT (2018-002207-34).

#### 2-4b. SAP version/Protocol version:

| SAP version | Date       | Protocol nr | Alterations                                                                                                                                                                                                |
|-------------|------------|-------------|------------------------------------------------------------------------------------------------------------------------------------------------------------------------------------------------------------|
| 4.0         | 15.04.2024 | V7          | 20. As-treated analyses added

27a. Clarification of statistical methods included in SAP                                                                                                             |
| 3.0         | 22.01.2024 | V7          | 7. Reference to protocol paper added

20. Intention-to-treat and per-protocol analyses added                                                                                                         |
| 2.0         | 15.05.2019 | V2          | 19a. Updated to match wording in latest protocol.

24a-c. Updated to match wording in latest protocol

29. Additional analyses updated to accommodate inclusion of questionnaires in the trial |
| 1.0         | 23.08.2018 | V1          |                                                                                                                                                                                                            |

## Section 2: Introduction

### 7. Background and Rationale

The increasing use of frozen embryo transfer (FET) underscores an urgent need to identify the best protocols for preparing the endometrium in FET Cycles.

The aim of this multicentre RCT is to assess the effect of progesterone supplementation in human chorionic gonadotropin (hCG) triggered modified natural cycle (mNC) FET and the effect of embryo thawing and transfer at hCG+6 or hCG+7 days, respectively.

A full description of study rationale can be found in the study protocol and protocol paper published in 2019.[1,2]

### 8. Objectives

(1) To assess if luteal phase support (LPS) in mNC-FET is superior to no LPS in terms of live birth rate per transfer and

(2) To assess if blastocyst warming+transfer 6 days after hCG trigger is superior to warming+transfer 7 days after hCG trigger in terms of live birth rate per transfer in mNC-FET.

## Section 3: Study Methods

### 9. Trial Design

Randomised, single-blinded, controlled, trial using a 2 x 2 factorial design.

Participants will be randomised 1:1:1:1 to the following four study groups:

A) Luteal phase progesterone and warming+transfer 6 days after hCG trigger

B) Luteal phase progesterone and warming+transfer 7 days after hCG trigger

C) No luteal phase progesterone and warming+transfer 6 days after hCG trigger

D) No luteal phase progesterone and warming+transfer 7 days after hCG trigger.

### 10. Randomisation

“Randomisation will be performed by a study nurse or a non-treating doctor using a randomisation program (dOxos CDS AB) on the day of the hCG trigger.

Randomisation will be performed 1:1:1:1. The randomisation program will take the following confounding factors into account; female age <37 or ≥37 years, number of previous oocyte retrievals, number of previous FET cycles, trial site and blastocyst Gardner score at the day of embryo freezing, to secure an equal distribution in the four study arms.”[1]

## 11. Sample Size

“A total of 604 patients are required to have an 80% chance of detecting, at a significance level of 5%, an increase in live birth rate to 31% in the intervention group from 21% in the control group. Sample size calculation does not need correction for the two interventions, as they are considered fully independent of each other.”[1]

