## 12. Framework

The study is designed as a superiority trial making the following comparisons:

Comparison I: Vaginal progesterone (group A+B) vs no vaginal progesterone (groups C+D).

Comparison II: Blastocyst warming+transfer day 6 after hCG trigger (group A+C) vs blastocyst warming+transfer day 7 after hCG trigger (group B+D).

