#### 19. Adherence and Protocol Deviations

**19a. Definition and assessment of adherence.**

Adherence to study interventions will be logged continuously throughout the trial.

Comparison I: Use of LPS vs no use of LPS

“Complete medicine accounts will be kept by the study nurses at each of the trial sites. All medication handed out to the patients will be recorded and patients are instructed to inform the study personnel about deviations in medicine administration and to deliver all medication packings, with or without remaining medicine, back to the study nurses after end of participation.

The study nurses at Rigshospitalet will keep the overall medicine accounts files of the study medication used in the project and collect all the medicine accounts from each of the trial sites after end of inclusion.”[1]

Comparison II: Timing of blastocyst transfer

Due to the nature of the intervention, it will not be possible for patients to deviate from the allocated intervention, as their blastocyst will be thawed, and blastocyst transfer scheduled, at the allocated day of blastocyst transfer. It might however happen that a participating study clinic cannot offer blastocyst transfer on the allocated day due to weekly closing days or bank holidays. In this case, the patient will be offered treatment on the previous or next day according to local routines. These patients will be included in the per-transfer, intention-to-treat and as-treated analyses, but excluded from the per-protocol analyses.

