## 20. Analysis Populations

Per-transfer (primary population): Women randomised, undergoing embryo transfer

Intention-to-treat: Women randomised.

As-treated: Women randomised, grouped according to treatment received.

Per-protocol: Women randomised, undergoing allocated treatment.

Women withdrawing consent to participate in the trial will be removed from all analyses.

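### Section 11's 604 is the bare analysed number: it leaves about two women in reserve and allows nothing for untransferred women, withdrawals or closing-day moves between the Comparison II arms

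*SAP*

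**What the plan says.** Section 11 (Sample Size) states: "A total of 604 patients are required to have an 80% chance of detecting" "an increase in live birth rate to 31% in the intervention group from 21% in the control group", at the 5% level. It does not say whether the 604 are women randomised or women transferred, and it names no allowance for loss or for a changed transfer day. The text is quoted from the protocol.

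Section 10 places randomisation on the day of the hCG trigger, six or seven days before the planned transfer. Section 20 then defines the main analysis set: "Per-transfer (primary population): Women randomised, undergoing embryo transfer". The same section removes women who withdraw consent from all analyses.

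The arms of Comparison II (section 12) differ by one day: A+C at trigger+6 and B+D at trigger+7. Section 19a says a clinic might be closed on the allocated day, because of a weekly closure or a public holiday, and that in this case "the patient will be offered treatment on the previous or next day according to local routines". On the analysis it says: "These patients will be included in the per-transfer, intention-to-treat and as-treated analyses, but excluded from the per-protocol analyses".

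**The concern.** A sample size calculated for analysed women, with almost nothing to spare, is set beside analysis rules that can only reduce the number analysed or narrow the contrast. Two mechanisms are involved.

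- **Fewer women analysed.** If 604 women are randomised, every woman without a transfer and every withdrawal takes the primary analysis below the calculated number, in both comparisons.
- **A smaller contrast in Comparison II.** Because the arms are one day apart, a trigger+6 woman moved to the next day receives the other arm's timing, and so does a trigger+7 woman moved to the previous day. Keeping them in their allocated group is proper randomised analysis, but it dilutes the difference.

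The per-protocol rule raises a related problem. A closure on trigger+6 removes women from A/C only, and a closure on trigger+7 removes women from B/D only. The two arms left are then drawn from different calendar days and, where opening days differ, from different mixes of sites.

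At stake is how a null result is read: against an 80% chance of detection that may not apply, and with a per-protocol analysis whose exclusions depend on the arm.

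**Working it through.** **Inputs from the SAP.** Rates 31% and 21%, level 5%, power 80%, total 604 (section 11). Allocation is 1:1:1:1 (section 9), so each marginal comparison has 302 v 302. Sidedness is not stated; the two-sided version reproduces the total.

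**Step 1: reproduce 604.** Pooled-variance formula without continuity correction, mean rate 0.26:

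n = [1.960 × √(2 × 0.26 × 0.74) + 0.842 × √(0.31 × 0.69 + 0.21 × 0.79)]² / 0.10² = [1.960 × 0.6203 + 0.842 × 0.6163]² / 0.01 = 300.8

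This rounds up to 301 per side, 602 in total. The next multiple of four is 604, which suits four groups. (Unpooled variance gives 598; a continuity correction gives 642; a one-sided test gives 474.)

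**Step 2: power at 302 per side.** Standard error under no difference = √(2 × 0.26 × 0.74 / 302) = 0.03570; under the alternative = √((0.31 × 0.69 + 0.21 × 0.79) / 302) = 0.03546.

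Power = Φ[(0.10 − 1.960 × 0.03570) / 0.03546] = 80.2%. The reserve is 604 − 602 = 2 women.

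**Step 3: loss before analysis (both comparisons, if 604 counts women randomised).** The SAP gives no rate, so the shares d are assumed. Analysed per side = 302 × (1 − d).

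| Assumed loss | Analysed per side | Power |
|---|---|---|
| 2% | 296.0 | 79.4% |
| 5% | 286.9 | 78.1% |
| 10% | 271.8 | 75.9% |

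**Step 4: crossover in Comparison II, 302 per side, no loss.** Two assumptions: the 10 points is the effect with every transfer on the allocated day, and women moved to a day belonging to neither arm keep their own arm's rate. With a share f crossing each way, the rates become 0.31 − 0.10f and 0.21 + 0.10f, a contrast of 10 × (1 − 2f) points.

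| Assumed crossover | Contrast (points) | Power |
|---|---|---|
| 2% each way | 9.6 | 76.8% |
| 5% each way | 9.0 | 71.4% |
| 7.1% each way | 8.6 | 67.1% |
| 5% in one arm only | 9.5 | about 76% |
| 14.3% in one arm only | 8.6 | about 68% (66% if the arm with the 21% rate is the one that crosses) |

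The last three sizes can be placed as follows. If a site closes one day in seven and trigger days are spread evenly, 1/7 = 14.3% of each arm moves. If half the moves land on the other arm's day, crossover is 7.1% each way. If the site always moves women in the same direction, only one arm crosses: with a next-day routine, trigger+6 becomes trigger+7 but trigger+7 becomes trigger+8; with a previous-day routine it is the reverse. The 5% one-arm row is a milder case of the same pattern.

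A 5% loss together with 5% crossover each way gives 69.2%.

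**Step 5: the per-protocol sets under the same one-day-in-seven assumption.** The SAP rule removes 1/7 of each arm, on different calendar days, leaving 6/7: 302 × 6/7 = 258.9 per side, power 73.8%. Keeping in both arms only women whose site was open on both trigger+6 and trigger+7 removes 2/7, leaving 5/7: 302 × 5/7 = 215.7 per side, power 65.9%. Both figures use the full 10-point contrast.

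**The case against.** The calculation contains no error; 604 follows from its inputs. Objective wording in section 8 is per transfer, so 604 may well mean women transferred, in which case Step 3 falls away. Section 11 is quoted from the protocol, which was not available here, and an allowance for recruitment may be given there. Even if 604 means women randomised, a 5% loss costs only about two points. All of this stands, and it makes the non-transfer part modest.

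A reader might infer more than the SAP supports, in four ways.

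- **That the plan makes 604 on-day transfers impossible, so true power must be below 80%.** Section 19a says only that a closing-day move might happen, and section 20 only defines populations. No rate is given for non-transfer, withdrawal or moves.
- **That Comparison II necessarily suffers more.** Section 19b expects missed progesterone doses, which may dilute Comparison I by an equally unknown amount.
- **That a weekly closure moves one woman in seven across in both arms.** With one closing day and a consistent direction, only one arm crosses. Crossover of that size in both arms would need two closing days or a direction that depends on allocation, and the SAP states neither.
- **That the 10 points is a full-adherence effect.** Section 11 does not say so. If the figure already includes some moves, Step 4 overstates the loss.

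The reporting plan also helps. Section 19d promises major deviations in the primary paper, section 19c counts a clinic's inability to follow allocation among them, and section 18 provides 95% confidence intervals. A careful reader can judge a null result from those. They do not correct the power statement itself or the arm-dependent exclusion. No bias from that exclusion has been demonstrated, since nothing shows that weekday or site calendar is prognostic; the point is that comparability is given up when it could be kept.

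**Conclusion.** The point holds in conditional form. The 80% in section 11 applies to about 604 analysed women with a full 10-point contrast, and it has a margin of about two women. It makes no allowance for non-transfer, withdrawal or the closing-day moves that the SAP itself provides for.

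The size depends on rates the SAP does not give. Non-transfer matters only if 604 counts women randomised, and is small up to about 5%. Crossover in Comparison II costs more per percentage point: 5% each way takes about nine points of power where a 5% loss takes about two. That rests on the 10 points being the full-adherence effect. The documents do not establish that power is in fact below 80%, nor which comparison is worse affected.

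The arm-dependent per-protocol exclusion follows from the wording of section 19a and needs no assumed rate.

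**What to change.** 1. **Section 11.** State that 604 is the analysed (transferred) number, and that 80% for Comparison II assumes transfer on the allocated day.
2. **Reporting.** Give power for each comparison at the actual number of transfers and, for Comparison II, at the actual share of each arm moved to the other arm's day.
3. **Per-protocol analysis of Comparison II.** Restrict both arms to women whose site was open on both trigger+6 and trigger+7. Trigger date and site calendar fix this before allocation, so the restriction cannot differ by arm.

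Items 1 and 2 cost SAP wording and possibly a less favourable power figure. Item 3 needs only trigger dates and site opening days, and no added patients, but it costs precision, which the SAP should state. If one day in seven is closed, about 5/7 of women remain rather than 6/7, with power of about 66% rather than 74%.

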## 12. Framework

The study is designed as a superiority trial making the following comparisons:

Comparison I: Vaginal progesterone (group A+B) vs no vaginal progesterone (groups C+D).

Comparison II: Blastocyst warming+transfer day 6 after hCG trigger (group A+C) vs blastocyst warming+transfer day 7 after hCG trigger (group B+D).

## 13. Statistical Interim Analyses and Stopping Guidance

No interim analyses are planned as it is assumed none of the interventions are at risk of harming the patients' chance of conceiving and giving birth.

## 14. Timing of Final Analysis

| Outcome                          | Timing of final analysis                                                                                                                                       |
|----------------------------------|----------------------------------------------------------------------------------------------------------------------------------------------------------------|
| Primary outcome           |                                                                                                                                                                |
| Live birth rate                  | Following the one-year follow-up of last patient enrolled in the trial with a verified clinical pregnancy and no record of pregnancy loss (one-year follow-up) |
| Secondary outcomes        |                                                                                                                                                                |
| Pregnancy rate                   | When the last patient participating in the trial has completed her pregnancy test                                                                              |
| Clinical pregnancy rate          | When all patients enrolled in the trial, with a positive pregnancy test, have attended their early pregnancy scan                                              |
| Pregnancy loss rate              | Following the one-year follow-up of last patient enrolled in the trial with a verified clinical pregnancy and no record of pregnancy loss (one-year follow-up) |
| Obstetric and perinatal outcomes | Following the one-year follow-up of last patient enrolled in the trial with a verified clinical pregnancy and no record of pregnancy loss (one-year follow-up) |

## 15. Timing of Outcome Assessments

All outcomes will be assessed at an individual level.

| Outcome                                 | Timing of outcome assessments                                                                                                                            |
|-----------------------------------------|----------------------------------------------------------------------------------------------------------------------------------------------------------|
| Primary outcome                  |                                                                                                                                                          |
| Live birth rate                  | Approximately one year after inclusion in trial (one-year follow-up) for all patients with a verified clinical pregnancy and no record of pregnancy loss |
| Secondary outcomes               |                                                                                                                                                          |
| Pregnancy rate                   | Assessed following the pregnancy test conducted at ovulation trigger + 16 days.                                                                          |
| Clinical pregnancy rate          | Assessed at the early pregnancy scan planned in gestational week 8 of all patients with a positive pregnancy test                                        |
| Pregnancy loss rate              | Assessed continuously in patients with a positive pregnancy test, depending on the time point of pregnancy loss                                          |
| Obstetric and perinatal outcomes | Approximately one year after inclusion in trial (one-year follow-up) for all patients with a verified clinical pregnancy and no record of pregnancy loss |

## Section 4: Statistical Principles

### Confidence Intervals and P-Values

#### 16. Level of statistical significance to be used.

A significance level of 5% will be used.

#### 17. Adjustment for Multiplicity

No adjustment for multiplicity will be conducted.

#### 18. Confidence Intervals

95% confidence intervals for mean differences, risk differences (RD) and adjusted risk differences (aRD) will be calculated.

#### 19. Adherence and Protocol Deviations

**19a. Definition and assessment of adherence.**

Adherence to study interventions will be logged continuously throughout the trial.

Comparison I: Use of LPS vs no use of LPS

“Complete medicine accounts will be kept by the study nurses at each of the trial sites. All medication handed out to the patients will be recorded and patients are instructed to inform the study personnel about deviations in medicine administration and to deliver all medication packings, with or without remaining medicine, back to the study nurses after end of participation.

The study nurses at Rigshospitalet will keep the overall medicine accounts files of the study medication used in the project and collect all the medicine accounts from each of the trial sites after end of inclusion.”[1]

Comparison II: Timing of blastocyst transfer

Due to the nature of the intervention, it will not be possible for patients to deviate from the allocated intervention, as their blastocyst will be thawed, and blastocyst transfer scheduled, at the allocated day of blastocyst transfer. It might however happen that a participating study clinic cannot offer blastocyst transfer on the allocated day due to weekly closing days or bank holidays. In this case, the patient will be offered treatment on the previous or next day according to local routines. These patients will be included in the per-transfer, intention-to-treat and as-treated analyses, but excluded from the per-protocol analyses.

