**19b. Presentation of adherence data.**

If gross inability to follow allocated study group is detected, data will be presented in publication reporting on the primary outcome.

It is expected that some patients will forget to administer one-several doses of their LPS during the trial, seeing as the medication is administered three times daily. While all deviations will be accounted for by the participating study clinics, minor deviations in adherence to study interventions will not be publicly reported.

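### One per-protocol set serves both factors, so, read literally, women moved by a closing day are lost from the progesterone per-protocol analysis for a reason unrelated to progesterone

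*SAP*

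**What the plan says.** SAP section 9 sets out the design: "Participants will be randomised 1:1:1:1 to the following four study groups". The groups combine progesterone or none with transfer 6 or 7 days after the trigger. Section 12 plans two comparisons on the margins: A+B against C+D for progesterone (Comparison I), and A+C against B+D for timing (Comparison II). Section 11 treats the two interventions as independent of each other.

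Section 20 lists four populations, with per-transfer as primary. The per-protocol entry is a single line, not split by factor: "Per-protocol: Women randomised, undergoing allocated treatment".

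Under its Comparison II heading, section 19a covers transfers shifted by a day because a clinic is closed: "These patients will be included in the per-transfer, intention-to-treat and as-treated analyses, but excluded from the per-protocol analyses".

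For progesterone, 19a describes medicine accounts and pack returns. Section 19b adds: "It is expected that some patients will forget to administer one-several doses of their LPS during the trial". It then says that minor deviations in adherence will not be publicly reported. Section 19c describes a major deviation as the patient or clinic being unable to comply with the allocated group.

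**The concern.** In a factorial trial, each margin asks its own question. Whether a woman's transfer took place on her allocated day says nothing about whether she followed her progesterone allocation. Each woman is allocated to a combined group, so the one-line definition in section 20, taken at its word, requires her to have followed both factors. The exclusion in 19a is then stated for the per-protocol analyses in general.

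Two losses follow:

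- A woman moved by a closing day is dropped from the per-protocol analysis of Comparison I for a calendar reason.
- A woman who did not follow her progesterone allocation is dropped from the per-protocol analysis of Comparison II, although her transfer took place on the right day.

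Neither exclusion makes the set a better measure of adherence to the factor being compared. Section 27e plans no sensitivity analyses, so the alternative populations are what a reader has for judging how robust the primary result is. Their membership should be settled, and no precision should be given up without need.

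**Working it through.** **Inputs from the SAP (section 11).** "A total of 604 patients are required to have an 80% chance of detecting" the stated effect, which is "an increase in live birth rate to 31% in the intervention group from 21% in the control group". The significance level is 5%. Allocation is equal on each margin, so 604 / 2 = 302 per side. Sidedness is not stated; two-sided is assumed.

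**Step 1: reproduce the stated sample size.** Pooled-variance formula, no continuity correction:

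n per side = [1.96 × √(2 × 0.26 × 0.74) + 0.842 × √(0.31 × 0.69 + 0.21 × 0.79)]² / 0.10²

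= [1.96 × 0.6203 + 0.842 × 0.6163]² / 0.01 ≈ 301 per side, or 602 in total. This agrees with the stated 604 for practical purposes.

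Power with 302 per side: Φ[(0.10 × √302 − 1.96 × 0.6203) / 0.6163] = Φ(0.847) = 80.2%.

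**Step 2: joint set, women moved by closing days.** The SAP gives no share moved, so a range is assumed, spread equally over the four groups and with no other exclusions. With a share f moved, n per side = 302 × (1 − f). Power uses the formula in step 1. The 95% half-width is 1.96 × √[(0.31 × 0.69 + 0.21 × 0.79) / n].

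| Assumed share moved | Women left in Comparison I | Power | 95% half-width (points) |
|---|---|---|---|
| 0 | 604 | 80.2% | 6.95 |
| 5% | 574 | 78.1% | 7.13 |
| 10% | 544 | 75.9% | 7.32 |
| 1 in 7 | 518 | 73.8% | 7.51 |
| 20% | 483 | 70.9% | 7.77 |

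The 1-in-7 row illustrates one closing day a week at every site, with triggers spread evenly over the week.

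**Step 3: set defined by factor.** Women moved by a closing day stay in Comparison I. This cause removes nobody, and the first row of the table applies at any share moved.

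**Step 4: the other direction.** If a share g of A+B did not follow the progesterone allocation, the joint set removes 302 × g women from Comparison II. For g = 10%, 604 − 30 = 574 remain (power 78.1%). For g = 20%, 604 − 60 = 544 remain (75.9%). These shares are also assumptions. A set defined by factor removes none of these women from Comparison II.

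**The case against.** The best defence is where the sentence stands. The exclusion in 19a comes under the Comparison II heading, and Comparison I has its own adherence text, so the authors may have meant only the timing analysis. That is possible, and it is why the joint reading is the literal one but not certain. It does not settle the matter, because section 20 offers no second set for Comparison I to use.

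A joint definition can also be defended for women allocated to one of four combined groups, in an analysis that is only supporting. That limits the weight of the point. It does not show any gain from the joint set when the comparisons are made on the margins.

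A reader might infer more than the SAP supports, in three ways:

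- **That closing days bias the progesterone comparison.** They follow the calendar and not the progesterone allocation, so both sides should lose women alike. Similarly, progesterone non-adherence takes women from A and B, which lie on opposite sides of Comparison II, so it does not in itself unbalance that comparison.
- **That any forgotten dose removes a woman, and so thins only A+B.** Section 19b follows its remark on forgotten doses with a reference to minor deviations, and 19c reserves major deviations for inability to comply with the group. Together they point to forgotten doses being minor. The lack of a numerical dose threshold is missing detail, not an error in itself.
- **That exclusion depends on the outcome, because pregnant women take progesterone for longer.** The SAP gives no treatment duration, so this cannot be shown from it.

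**Conclusion.** The point holds in a limited form. As written, one per-protocol set and an unrestricted exclusion remove women from each comparison for reasons that belong to the other factor. For closing days the consequence is lost precision in Comparison I. At an assumed 5% moved, about 30 women and 2 points of power are lost; at an assumed 20%, about 121 women and 9 points. The true share is not in the SAP, which says only that such moves might happen. The power figures also assume a two-sided 5% test, the planning rates of section 11 and equal loss across groups.

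The per-transfer primary result, the intention-to-treat result and the sample size do not change. This is worth correcting because the change is simple and removes an ambiguity in a supporting analysis, not because the main conclusion is at risk.

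**What to change.** In sections 19a and 20, define per-protocol separately for each factor:

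- **Comparison II:** women whose transfer took place on the allocated day, regardless of progesterone adherence.
- **Comparison I:** women with no major deviation, in the sense of 19c, from the progesterone or no-progesterone allocation, regardless of transfer day. Section 19c speaks of the allocated group as a whole, so the new text should say that only the progesterone part counts here.

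In 19a, limit the closing-day exclusion to the per-protocol analysis of Comparison II.

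When making this change, the trial team can also confirm, before outcome data are opened, that the forgotten doses foreseen in 19b count as minor and do not remove a woman from the set.

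The cost is a change of SAP wording. The two comparisons will then have different per-protocol denominators, which the results tables should show.

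### The per-protocol rule for closed transfer days leaves the hCG+6 and hCG+7 arms with different trigger weekdays, and no planned set gives a randomised comparison of the two timings as actually delivered

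*SAP*

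**What the plan says.** Section 10 places randomisation "on the day of the hCG trigger". Section 12 defines Comparison II as groups A and C (transfer at hCG+6) against groups B and D (transfer at hCG+7).

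Section 19a, under Comparison II, allows that a clinic "cannot offer blastocyst transfer on the allocated day due to weekly closing days or bank holidays". In that case "the patient will be offered treatment on the previous or next day according to local routines". Women moved in this way are "included in the per-transfer, intention-to-treat and as-treated analyses, but excluded from the per-protocol analyses".

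Section 20 names the primary set, "Per-transfer (primary population): Women randomised, undergoing embryo transfer", and adds three others: all women randomised, women grouped by the treatment they received, and "Per-protocol: Women randomised, undergoing allocated treatment".

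The adjustment covariates in section 27b do not include trigger weekday or closing-day status. Section 27e plans no sensitivity analysis.

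**The concern.** The trigger date is fixed when a woman is randomised, and regular closing days and bank holidays are normally known in advance. Whether hCG+6, hCG+7, both or neither can be offered is therefore in effect a baseline fact about her. The per-protocol rule does not use it as one. It looks only at the day she was allocated, so two women with the same trigger date at the same site can be treated differently: one is excluded and the other kept, depending on their arm.

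Exclusion thus depends on trigger weekday and allocation together, and the arms that remain are no longer balanced on trigger weekday by design. If weekday, or anything that goes with it, is related to live birth, the per-protocol estimate of the timing effect is biased.

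The other sets do not fill the gap. Objective 2 asks about transfer 6 against 7 days after trigger. Where transfers are moved, the sets that follow allocation compare two scheduling policies, and the set that follows actual timing does not follow allocation.

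**Working it through.** **Inputs.** From the SAP: randomisation on the trigger day (section 10); exclusion when the allocated day is closed (19a); 604 women, 31% against 21% live birth, 80% power and 5% significance level (sections 11 and 16). Assumed, because the SAP gives no rates: triggers spread evenly over the week, and either one closing day (Sunday) or two (Saturday and Sunday) at every site. These are upper scenarios; the lower end is no closure. Per-protocol losses for other reasons are ignored.

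**The plan's own figure.** A two-sided comparison of 31% with 21%, pooled variance under the null and no continuity correction:

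n per arm = [1.96·√(2·0.26·0.74) + 0.842·√(0.31·0.69 + 0.21·0.79)]² / 0.10² ≈ 301, or 602 in total.

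This agrees with 604 up to rounding. Power at 302 per arm is 80.2%.

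**Which trigger weekdays each arm loses.** A trigger on weekday w has hCG+6 on the weekday before w in the following week, and hCG+7 on w itself.

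| Closed | hCG+6 arm loses | hCG+7 arm loses | Both days open | Only in hCG+6 arm | Only in hCG+7 arm |
|---|---|---|---|---|---|
| Sunday | Mon | Sun | Tue to Sat (5/7) | Sun | Mon |
| Saturday and Sunday | Sun, Mon | Sat, Sun | Tue to Fri (4/7) | Sat | Mon |

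With one closing day, each per-protocol arm keeps six weekdays and one of them is unmatched: 1/6. With two, each keeps five and one is unmatched: 1/5. With weekend closure, Sunday triggers leave both arms and so cause no imbalance.

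**Bias in per-protocol.** The matched weekdays cancel, so bias = (live-birth gap between the two unmatched weekdays) × 1/6 or 1/5.

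| Assumed weekday gap | One closing day (×1/6) | Two closing days (×1/5) |
|---|---|---|
| 2 points | 0.3 | 0.4 |
| 5 points | 0.8 | 1.0 |
| 10 points | 1.7 | 2.0 |

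**Size of a set fixed at baseline.** Keep a woman if both hCG+6 and hCG+7 were open for her trigger date, whatever her allocation. Power is for 31% against 21%.

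| Closing days at all sites | Per-protocol | Both days open |
|---|---|---|
| One | 604 × 6/7 ≈ 518 (73.8%) | 604 × 5/7 ≈ 431 (65.9%) |
| Two | 604 × 5/7 ≈ 431 (65.9%) | 604 × 4/7 ≈ 345 (56.3%) |
| None | 604 | 604 |

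**What the sets that follow allocation estimate.** With one closing day, a site that always moves to the next day sends its moved hCG+6 women to hCG+7 and its moved hCG+7 women to hCG+8. A site that always moves to the previous day sends them to hCG+5 and hCG+6. Either way, half of those moved land on the other arm's day. If women at hCG+5 or hCG+8 keep their arm's rate (assumed), a true 10-point difference becomes 10 × (1 − 1/7) = 8.6 points, with power of about 67% at 604 women.

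**The case against.** The strongest reply is that this concerns a secondary set. Objective 2 is framed per transfer, the per-transfer population is primary, and women with moved transfers stay in it and in intention-to-treat. Every per-protocol set gives up some protection from randomisation, and the SAP does not claim otherwise. Any trial with non-adherence lacks a randomised comparison of treatment as delivered. Sections 19c and 19d also treat a clinic's failure to follow allocation as a major deviation, to be reported in the primary paper. All of this stands, and it limits the point to an improvement. It does not remove it, because here the main cause of non-adherence can be known at baseline, so a randomised comparison is available at little cost.

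Three stronger readings are tempting and are not supported:

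- A reader might infer that the primary analysis is biased or underpowered. It follows allocation among women transferred and compares scheduling policies. The 8.6-point figure holds only if every site closes weekly; the SAP says that closure might occur and gives no frequency.
- A reader might infer that the per-protocol estimate is materially biased. Nothing in the SAP shows that trigger weekday is prognostic, or that clinics choose it in a way related to prognosis.
- A reader might infer that the per-protocol analysis of Comparison I is damaged too. The exclusion sentence stands under Comparison II, so its reach to Comparison I is a matter of reading. If it applies, about 604 × 1/7 ≈ 86 to 604 × 2/7 ≈ 173 women are lost under the same assumptions. Groups A and B together, and C and D together, each contain both timings, so this costs precision and does not bias. For women allocated to combined groups, one common per-protocol set is defensible.

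**Conclusion.** The point holds as a modest weakness in a secondary analysis. Wherever a site has fixed closing days, the rule in section 19a leaves each per-protocol arm with one trigger weekday that the other lacks, and neither the covariates nor any planned sensitivity analysis repairs this. None of the four sets gives a randomised comparison of actual hCG+6 against actual hCG+7.

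The unmatched weekday is 1/6 to 1/5 of each per-protocol arm, assuming evenly spread triggers and closure at all sites; with fewer closing sites it is less. The bias is about 0.3 to 2 points for assumed weekday gaps of 2 to 10 points, against a design difference of 10 points. It is probably small, and it is zero if weekday is not prognostic or no transfer is moved. The primary per-transfer analysis is unaffected by this defect.

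**What to change.** In sections 20 and 27e, add a supplementary analysis for Comparison II: women whose trigger date and site calendar left both hCG+6 and hCG+7 open, with the same restriction in both arms, analysed as allocated. Fix each site's closing days from its calendar without reference to allocation or outcome. Report the number of women moved by arm, with the actual interval from trigger to transfer, so that readers can see how much the issue matters. The present per-protocol analysis can stay, described as not protected by randomisation.

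The cost is SAP wording, one extra analysis and the collection of past closing days per site, which the SAP does not say are recorded. The trigger date follows from the randomisation date. The set is smaller than per-protocol, by about 86 women under either closing pattern at all sites, so its interval will be wider and it should be read as supportive. Deviations from the allocated day for reasons other than closure would remain in it.

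Optionally, state whether a moved transfer also removes a woman from the per-protocol analysis of Comparison I; keeping her there would gain precision only. None of this changes clinical scheduling.
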